### Dropout and data retention

Participants that want to exit the study can do so at any given time by informing the study PI or the therapist providing the treatment. Their names and contact information are provided in the consent form. In case of dropout, the participant is asked if they are willing to report why they want to exit the study. If information regarding reason for exit of the study is provided, the information is registered on a dedicated drop-out sheet. Unless the participant requires all their data deleted, data is still included in the intention-to-treat (ITT) analyses.

### Statistical methods

Intention-to-treat (ITT) analysis will be applied, using data from all randomized participants, regardless of whether they complete the intervention. Descriptive statistics will be reported for sample description and outcome measures. The effect of the intervention will be assessed by linear mixed-effect models fitting the primary and secondary continuous outcome variables to account for repeated measurements by patients. Time (T1, T2, and T3) and time-by-treatment interaction will be used as fixed effects in these models. The main effect of group will be included to control for potential baseline differences. Based on the linear mixed effect models, we will estimate mean values with 95% confidence intervals (CI) for the three time points (T1, T2, and T3) for each treatment group. We will also estimate the mean between-group changes from T1 to T3. These models account for missing data on individual time points, thus obviating the need to impute missing values. We will preregister the analytic strategy. The role of self-efficacy on the effect of hypnosis will be explored with linear regression models. No interim analyses will be performed.

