## Methods

### Trial design

The study is organized as a randomized controlled superiority trial with parallel group design and three arms including (1) an intervention group, (2) an active control group, and (3) a passive control group. Participants will be randomly allocated in a 1:1:1 ratio to either of the three groups. The intervention group will receive four weekly 1-h sessions with hypnosis treatment (induction + hypnotic suggestion), while the active control group will receive four weekly 1-h sessions of non-targeted hypnotic suggestions (induction + mindfulness-based instructions) to factor out nonspecific treatment effects. The passive control group will be assessed at the same time points as the other two groups to isolate retest effects. Each participant will be assessed three times: (1) at baseline (T1), (2) immediately after the intervention which is 5 weeks post baseline (T2), and (3) 25 weeks after baseline (T3, follow-up). The study will follow the CONSORT statement facilitating complete and transparent reporting and aiding critical appraisal and interpretation (http://www.consort-statement.org/). This study expands the design of Lindeløv et al.’s study through a larger number of participants, the inclusion of far-transfer outcome measures, and the exploration of potential underlying mechanisms of treatment effects. Because this study is performed in collaboration with the principal investigator of the original study [4], we rely on learnings from that study rather than conducting a small-scale pre-study pilot and/or feasibility trial. The intervention will be based on the hypnosis scripts by Lindeløv et al. translated from Danish to Norwegian [4].

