### Sample size and power calculations

Although Lindeløv et al. [4] found large treatment effects, their novel and unreplicated nature causes us to design a study that will also be informative with medium effect sizes. We set a sample size so that we can detect clinically meaningful changes of 0.5 SD on the primary outcome measures, i.e., the WAIS-IV Working Memory Index and BRIEF-A Working Memory Scale. Computed in G*Power, the group × time within-between interaction effect would require 22 completers in each group for a medium-sized effect (*ηp*^2^ = 0.07), 1% significance level (due to corrections for multiple testing), and a power of 90%. Allowing for a 20–25% drop-out rate brings the required sample to 30 participants per group, i.e., a total of *n* = 90. The success criterion in this study is thus defined as medium effect sizes (*ηp*^2^ = 0.07).

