### Randomization and blinding

Eligible patients will be identified by the study PI (author [name]) from the department of cognitive rehabilitation (KReSS) at Sunnaas Rehabilitation Hospital. After baseline assessment, participants will be randomly allocated to either of the three groups. The randomization sequence will be generated electronically in STATA by an independent statistician.

The allocation sequence will be stored in a database that can only be accessed by the study’s principal investigator. It will not be possible to blind neither the participants nor the PhD candidate who will conduct the hypnotic suggestions. Outcome assessments will, however, be blinded in that a person external to the study will perform these without knowledge of group allocation. Our research group has extensive experience in managing blinded clinical trials, and we are confident that this can be conducted in a truly blinded way without contamination. Data analysis will also be blinded in that fake ID numbers will be assigned to participants in the final database, ensuring that the statistical analysis is performed without knowledge of true group content until after the analyses are finalized.

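### Giving each arm its own baseline mean does not adjust for baseline, and costs precision that the pre-randomisation T1 measurement could supply

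*Protocol article*

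**What the plan says.** The Statistical methods section of the protocol article specifies linear mixed models for the continuous primary and secondary outcomes. On the fixed effects it says: "Time (T1, T2, and T3) and time-by-treatment interaction will be used as fixed effects in these models". It then adds: "The main effect of group will be included to control for potential baseline differences". T1 is therefore one of the response rows, and each arm has its own T1 mean. The section promises model-estimated means with 95% confidence intervals at all three time points for each group, and on the treatment contrast says: "We will also estimate the mean between-group changes from T1 to T3".

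On timing, the section Randomization and blinding says: "After baseline assessment, participants will be randomly allocated to either of the three groups". Allocation is 1:1:1 (Trial design). The sample size section states that "the group × time within-between interaction effect would require 22 completers in each group", at a 1% level and 90% power, raised to 30 per group for 20–25% dropout. Neither section gives a correlation between time points, and the article describes no model in which baseline is a covariate or the T1 means are held equal.

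**The concern.** The reason given for the group term does not fit the design. Because T1 precedes allocation, any difference between arms at T1 is chance. A free T1 mean per arm does not remove the effect of that chance difference on the result. It subtracts the whole observed baseline gap, as a change score does, although only a fraction rho of the gap (rho being the T1–T3 correlation) is expected to persist at follow-up. The remaining 1 − rho enters the estimate as noise.

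At stake is precision. The trial plans for 22 completers per arm at a 1% level, so variance that can be removed with data already collected is worth removing. The model and its rationale are stated explicitly, so this is a stated choice and not a detail left to an analysis plan.

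**Working it through.** **Inputs from the protocol article.** Three arms, 1:1:1; T1 before randomisation; T1, T2 and T3 as responses with time, time-by-treatment and group; 22 completers and 30 randomised per arm; 20–25% dropout; partial eta squared 0.07; 1% level; 90% power.

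**Assumed.** Correlation rho between any two time points, 0.5 to 0.9, with equal variances σ² over time (compound symmetry).

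**1. The plan's own sample size.** For the G*Power within-between interaction, f² = 0.07/0.93 = 0.0753 (f = 0.274) and the noncentrality is f²·N·m/(1 − rho), where N is the total number of patients and m the number of measurements. With three groups, m = 2 and rho = 0.5, 22 per group gives 0.0753 × 66 × 2/0.5 = 19.9 on 2 and 63 degrees of freedom, and power 0.919. The smallest n reaching 90% is 21 per group, or 22 if f is rounded to 0.27. Then 22/0.75 = 29.3, so 30 per group. The stated figures reproduce under these settings. They are not the only ones that do so: two groups with three measurements also gives 21 to 22. Three groups with three measurements at rho 0.5 gives 17.

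**2. What the planned contrast estimates.** With complete data and a free mean in every arm-by-time cell, the T1–T3 interaction equals the difference between arms in mean change. Mixed models fitted to four simulated data sets agreed with the raw difference to about 1e-15.

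**3. Variance with complete data, n per arm.**
- Planned: 2 × 2(1 − rho)σ²/n.
- Common T1 mean, or T1 as covariate: 2(1 − rho²)σ²/n.
- Ratio: (1 + rho)/2.

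**4. Variance with 25% dropout.** Take the case where dropouts have T1 only, with n = 30 randomised and c = 22.5 completers per arm.
- Planned: 2σ²[(1 − rho²)/c + (1 − rho)²/n].
- Common T1 mean: 2σ²(1 − rho²)/c.
- Ratio: (1 + rho)/[(1 + rho) + 0.75(1 − rho)].

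At rho 0.5 the ratio is 1.5/(1.5 + 0.375) = 0.80. If the dropouts are instead seen at T2 and missed only at T3, exact generalised least squares gives 0.796, 0.879, 0.919 and 0.960 at the four values of rho, which is nearly the same.

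| rho (assumed) | Ratio, complete | Variance saved | Ratio, 25% dropout | Variance saved |
|---|---|---|---|---|
| 0.5 | 0.75 | 25% | 0.80 | 20% |
| 0.7 | 0.85 | 15% | 0.88 | 12% |
| 0.8 | 0.90 | 10% | 0.92 | 8% |
| 0.9 | 0.95 | 5% | 0.96 | 4% |

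**5. In the plan's own terms.** On the set-up of step 1 (rho 0.5, two measurements, complete data), dividing the variance by 1/0.75 raises power at 22 per group from 0.919 to 0.980. Equivalently, 17 instead of 21 per group give 90%.

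**The case against.** The planned model is a standard longitudinal specification. It targets the contrast that the protocol names, matches the interaction used for the sample size, is unbiased under randomisation and keeps its type I error. The article never claims ANCOVA adjustment. All of this stands, and it makes the point one of efficiency and not of validity.

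Four stronger readings are tempting, and the protocol does not support them:

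- **Chance imbalance biases the result.** It does not. Imbalance averages to zero over randomisations and is already in the standard error. As an illustration, a 0.3 SD baseline gap at rho 0.7 moves the planned contrast by 0.3 × 0.3 = 0.09 SD. That is less than half its standard error of sqrt(4 × 0.3/30) = 0.20 SD with 30 per arm. This is the same loss of precision seen in one data set, not a second harm.
- **The contrast is a raw change score in this trial.** That is exact only with complete data. The protocol expects 20–25% dropout and keeps incomplete patients in the model, so the dropout columns of the table are the realistic ones.
- **The choice of model is what limits power.** Power for a pairwise 0.5 SD difference is a different calculation from the planned omnibus interaction. At rho 0.5 with 22 per arm and a 1% level, the change of model moves it only from about 16% to 23%. How 0.5 SD relates to the stated partial eta squared is a separate question.
- **The change has no downside.** The common-mean constraint rests on equal true T1 means, hence on concealed allocation. According to Randomization and blinding, the role that identifies eligible patients also has sole access to the allocation sequence. Concealment is therefore not assured.

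**Conclusion.** The point holds as a loss of precision. The group main effect does not deliver the baseline control given as its reason, and the planned T1–T3 contrast has more variance than one that uses baseline properly. The excess removed by adjustment is about 4% to 20% of the variance with 25% dropout, and 5% to 25% with complete data, over assumed correlations from 0.9 down to 0.5. It is small if the outcome is highly stable over time, and material at the correlation of 0.5 that reproduces the plan's sample size.

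These figures assume compound symmetry and equal variances, and ignore the small cost of estimating the regression on baseline. The planned analysis remains valid, so this is an improvement that should be made and not a defect that would undermine the result.

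**What to change.** Replace the sentence on the group main effect with text such as:

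> *Because T1 is measured before randomisation, the model constrains the arms to a common T1 mean: fixed effects are time, and time-by-treatment at T2 and T3 only, with no group main effect.*

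Alternatively, model T2 and T3 as outcomes with the T1 value as a covariate, allowing its coefficient to differ by time.

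Two further edits are needed:

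1. Amend the sentence that promises model-estimated means at T1 for each group. Under the constraint these are identical by construction, so report the observed T1 means per arm descriptively and model-based means at T2 and T3.
2. Secure the assumption. Keep the allocation sequence from whoever identifies and enrols patients, or use the T1-covariate form, which does not impose equal T1 means. Neither form repairs a selection effect that T1 does not capture.

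The cost is a few lines of text and model code, with no new data. The common-mean form keeps patients who have only T1 data, in line with the intention-to-treat statement. The covariate form drops them, and the article should then say so. The change belongs in the preregistered analytic strategy, before treatment groups are revealed to the analyst.

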### Ethical issues

The intervention will be carried out in accordance with guidelines from the Norwegian Society of Clinical Evidence-Based Hypnosis (NFKEH) by a clinical psychologist educated in hypnotherapy. Written, informed consent to participate will be obtained from all participants. The study will be conducted in accordance with the Declaration of Helsinki and the Vancouver recommendations for the conduct, reporting, editing, and publication of scholarly work in medical journals. The study has been approved by the Regional Committee for Medical and Health Research Ethics (approval number 216495) and the Norwegian Center for Research Data (NSD) (approval number 291031). The research is registered and made public at the Clinical Trials and Open Science Framework.

### Dissemination plans

The study results will be presented at Norwegian and international conferences in neurology, brain injury, and rehabilitation and in various arenas in which the Norwegian Union of Stroke (NFS) is active. The study results will be disseminated in Norwegian academic environments, and popular scientific presentations will be given. The results will also be communicated to the public through commercial channels like newspaper articles and social media. A dissemination strategy will be established in collaboration with the user panel who will actively participate in disseminating the findings and their relevance for patients through their channels. Given the close collaboration between Sunnaas Rehabilitation Hospital and other rehabilitation centers in Norway, we are well-positioned to communicate findings to other hospitals and stakeholders. Moreover, the Norwegian Society of Clinical Evidence-Based Hypnosis (NFKEH) provides education in hypnosis to health personnel subjected by the Norwegian Health Personnel Act. Since the head of NFKEH participates in this study, clinical hypnosis education of neurorehabilitation professionals will be provided.

## Discussion

The potential impact of applying hypnosis in cognitive rehabilitation is substantial. Deficits in WM are one of the most common challenges after ABI [3] and play a critical role in post-injury outcome [29]. Still, state-of-the-art approaches within WM rehabilitation have not been able to produce clinically relevant effects on real-life functioning for the affected patients [19]. In addition, today’s ABI rehabilitation is often time-consuming and requires hospitalization. As described by, e.g., Cicerone and colleagues [12], there is a need for more effective cognitive rehabilitation methods. Long-standing empirical evidence demonstrates that hypnosis is an effective therapeutic technique for a wide range of conditions [23], including in altering cognitive functions and improving WM in healthy adults. These findings are supported by changes seen in functional MRI [58] and event-related potentials [35]. Recent explorative research has suggested a promising efficacy of hypnosis in improving WM capacity in patients with ABI [4]. However, these findings are in need of replication in studies applying scientifically rigorous designs, and there is a need to understand potential underlying mechanisms of change.

Building on the strong results in the Danish single trial, we will aim at replication and expansion of the study in a Norwegian context. The initial study will be expanded in terms of the number of participants, injury characteristics will be included, and outcome measures of relevance to real-life functioning and possible underlying mechanisms of change will be explored. Self-efficacy is generalizable by nature (self-efficacy gained from mastery experiences in one situation generalizes to others); thus, WM rehabilitation effects are expected to generalize and transfer to other domains in daily life.

If previous findings are replicated, and transfer effects documented, patients may have improved WM capacity, including everyday WM, improved activities of daily living, self-efficacy, psychological well-being, and quality of life. These factors are critical to independence and may in turn affect the need for community support, community integration, and return to work. The intervention is manual based and short (four sessions) and is conducted in an outpatient clinic. Hypnotic interventions are typically brief, cost-effective, suitable for both in- and outpatients, for adolescents and adults, and can be learned easily; suggestions can be administered either by another person (hetero-hypnosis) or self-administered (self-hypnosis), adding portability to the mix of benefits. As the study that is being replicated is the only one to test hypnosis in rehabilitation of WM, a lack of replication, i.e., null findings, would also be highly informative to the field. Regardless of outcome, this study can provide valuable insights to other research groups and inform future studies. Study findings may inform future studies exploring the use of clinical hypnosis in other areas of rehabilitation, such as mild TBI (i.e., post-concussion symptoms), and in other neurological conditions where WM deficit is prominent, such as multiple sclerosis and Parkinson’s disease. A next step could also be to explore potential effects beyond the domain of WM, as studies have shown that self-efficacy is associated with mental health [27], quality of life [26], functional independence [28], and community integration [29]. This study thus has the potential to influence how we understand the clinical significance of psychological factors, like self-efficacy, on functioning after ABI. If successful, our ambition is to provide recommendations and materials to implement hypnotic suggestion as an adjunct treatment following ABI in Norwegian rehabilitation clinics.

### Trial status

The study was approved by the Regional Committee for Medical and Health Research Ethics in May 2021 and funded by Foundation Dam in December 2021. Recruitment for the RCT began at Sunnaas Rehabilitation Hospital in October 2022 and will end when we have enrolled the estimated sample size of 90, estimated June/July 2024.

### Plans for communicating important protocol modifications

Protocol modifications of importance will be reported to the Data Protection Office at Sunnaas Hospital, and amendments will be made to the trial registry (ClinicalTrials.gov) and Open Science Framework.

## Data Availability

Data will be stored electronically on a secure research server at Sunnaas Rehabilitation Hospital. The data will be kept for 5 years after the end of the project for control reasons. All principal investigators will be given access to the cleaned data sets. Access to data is regulated by Norwegian laws regarding data protection and research ethics.

## Abbreviations

ABI: Acquired brain injury
WM: Working memory
ADL: Activity of daily living
RCT: Randomized controlled trial
CATS: Cognitive activation theory of stress
NFKEH: The Norwegian Association of Clinical Evidence-based Hypnosis
ITT: Intention to treat
WAIS-IV: Wechsler Adult Intelligence Scale–Fourth Edition
TMTA: Trail Making Test Part A
TMTB: Trail Making Test Part B
CVLT-II: California Verbal Learning Test–Second Edition
BRIEF-A: Behavior Rating Inventory of Executive Function–Adult version
TBI-SE: The Traumatic Brain Injury Self-Efficacy Questionnaire
MSEQ: The Memory Self-Efficacy Questionnaire
HSCL: The Hopkins Symptom Checklist
QOLIBRI: Quality of life
PCRS: Patient Competency Rating Scale
Part-O: The Participation Assessment with Recombined Tools-Objective
